### Effectiveness outcomes

The primary outcome measure is the percent of patients who complete the tele-HS within 2 months of their PCP visit. Although in-office tele-HS may have a higher compliance rate than at-home tele-HS, the failure rate may be greater among those who proceed with in-home HS as their compliance to complete the HS at home could be motivated by suspected hearing loss. Our secondary effectiveness outcomes measured within 4 months of the failed tele-HS include the:
percent of patients who schedule follow-up diagnostic testing,percent of patients with an identify hearing loss with the tele-HS who attend the specialty visit for follow-up diagnostic audiologic testing,percent of patients with an identified hearing loss with the tele-HS who completed a plan for appropriate hearing loss intervention if indicated, andaccuracy of assessment for red flag conditions comparing PCP and audiologist evaluations versus an otolaryngology provider evaluation (gold standard).

We will also explore the association of cerumen impaction with pure-tone thresholds.

### Barriers to implementation

#### Attitudes and perceptions

Data are sought to describe the attitudes of patients and the perceived attitudes of communication partners regarding hearing loss. PCPs record patients’ subjective assessment of the presence or absence of significant hearing impairment. All patients in primary care are asked to complete two questionnaires either during the index office visit or at home, returning them with a pre-addressed and stamped envelope. The Attitudes towards Loss of Hearing Questionnaire for Non-Hearing Aid Users (ALHQ) is a 22-item instrument that measures attitudes on five subdomains: denial of hearing loss, negative associations, negative coping strategies, manual dexterity and vision, and hearing-related esteem [35–37]. Each item is scored by the patient on a 5-point Likert scale indicating level of agreement (strongly disagree, neither agree nor disagree, to strongly agree). The Significant Other Scale for Hearing Disability (SOS-HEAR) questionnaire measures the perceived attitudes of communication partners regarding hearing loss [38]. Patients complete the 27 items based on their partner’s perspective, responding to each item on a 5-point Likert scale for no problems (=0) to a complete problem (=4). The instrument is scored to assess the effects of hearing impairment on the significant other in the following domains: changes to communication, communication burden, relationship changes, going out and socializing, emotional reactions to adaptations, and concern for the partner. Attitudes are explored for their association with willingness to pursue HS, diagnostic testing, and consideration of intervention.

Sixteen focus groups are planned to collect data that will to provide context to the questionnaire results from the main study. These groups will include 128–160 patients, communication partners, clinic staff and healthcare clinicians across study groups and clinical sites. Discussions aim to understand attitudes and perceptions that may support or impede pursuit of hearing health care.

#### Cognitive function

PCPs are asked to assess cognitive function and comment on functionality using a 3-point scale (normal, mildly impaired, moderately-severely impaired). We will examine if successful completion of the tele-HS is possible for those with mild or moderately-severe cognitive impairment.

#### Costs of primary care intervention

Direct costs for each primary care intervention group and the individual strategies are calculated with costs of the educational material, tele-HS, and estimated cost of PCP time to educate and encourage the patient using a guided script (designed to be less than 3 min). Indirect costs for in-clinic HS include cost of the space used and staff time to direct patients to the room for the tele-HS.

### Statistical considerations

The primary analysis is based on the anticipated 660 patients who are deemed eligible and receive a study packet in the main study (R33 phase). In each of six practices, it is expected that 110 patients will receive a study packet, with two practices per intervention arm (*N* = 220 patients in each group). Due to the anticipated high rate of screen failures and withdrawals, we plan to approach up to 2000 patients (completed self-screening study eligibility forms) to meet the goal of 660 study packets distributed to eligible patients.

The primary outcome measure is the proportion of patients in each group who dial the phone number and complete the test within 2 months of their PCP visit. To test efficacy, Groups 1 and 2 will be compared to Group 3. Patients who complete the tele-HS outside of the 2-month window are not included in this primary analysis but are included in the per protocol analysis.

Secondary outcome measures will assess if there are group differences in the proportion of patients in all groups who: a) schedule, b) complete the visit for diagnostic audiologic testing, and subsequently, c) complete a plan for appropriate hearing loss intervention, if indicated, within 4 months of initial hearing screening.

#### Analysis for the primary outcome

The difference in the Group proportions in test completion will be examined for the primary outcome by a test of proportions. If there is an overall difference in rates of test completion, follow-up pairwise contrasts will be conducted to assess which groups differ significantly, comparing Group 3 vs. Groups 1 and 2, and, secondly, Groups 1 vs 2. Although every effort will be made to balance practice populations, we realize that practices may differ in the attributes of recruited patients. To control for baseline group differences, in follow-up sensitivity tests, we will assess if the differences in site, demographic, and comorbid conditions impact the observed group differences by multinomial logistic regression.

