### Patient recruitment and informed consent

Duke University serves as the study coordinating center for all research activities and is responsible for communicating across all sites and patients. Study approval from the Duke University Institutional Review Board (IRB) includes a waiver of consent due to participation having minimal risk and that it would not adversely affect individual welfare or patient rights. Study information provided to participating patients includes all elements of informed consent; however, written or verbal consent are not obtained or required. Personal identifiers are not stored with study data to protect confidentiality of patient during and after the trial. The pragmatic study design is dependent on preserving clinical flow. Obtaining written consent is not practical due to the large sample size per primary care practice.

A total of 955 subjects will be screened for eligibility to enroll 660 patients for the PCP aim. These 660 patients will be across six sites, 110 per practice in each of the six participating practice sites, two practices per intervention arm (*N* = 220 patients per group). Prospective enrollment is scheduled at each site based on the number of patients age 65–75 years, and participating provider schedules on a given day, until a total of 110 patients are enrolled. A member of the clinical care team first introduces the study to prospective patients. Either a member of the clinical care team or the study coordinator then gives the study informational consent page along with the self-screening study eligibility form to the patient. Patients have the option to participate; completing the study eligibility form implies patient consent. Patients who meet eligibility based on responses in the form are considered enrolled and receive a study packet appropriate for the intervention group to which that practice site is assigned.

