This study will establish evidence for conditions that should be contraindicated for hearing aid fitting and the impact of the most common red flag condition, cerumen, on hearing thresholds. Although the FDA has eliminated the requirement for medical evaluation of red flag conditions as it was in place without evidence to support it, we are still without research on these conditions as contraindications. The ‘red flag’ requirement for education of potential hearing aid users remains in place to ensure users are aware that there may be a medically treatable cause of their hearing loss. Our findings will help inform both practice and policies for audiologists, hearing aid dispensers and labeling of amplification devices.

As part of our implementation-effectiveness design, we chose not to randomize the patients or the sites for pragmatic reasons. Patient randomization to the intervention would mean that all clinics would have to be able to employ each screening strategy. In a real-world scenario, clinics will likely implement only one screening strategy. Clinic randomization is also not performed due to budget limitations for involving a high number of clinics and an unknown intra-class correlation for an adequately-powered cluster randomized trial, which would require at least 10 clinics per intervention arm. Site-level implementation allows us to train providers and measure costs of implementing a new approach as part of standard of care for this patient population. A site-level design increases pragmatism, feasibility of PCP engagement, and simplifies the patient recruitment process in comparison with a patient-level or patient-randomized design. We aim to achieve balance in site-level characteristics (PCP specialty, number of providers and eligible patients) and the number of patients is held constant across sites and interventions arms. However, we will plan to evaluate for imbalance in patient characteristics (race/ethnicity, sex) of study participants and non-participants between groups, and demographics of the study sample (approached, declined, enrolled) to the overall practice demographics for this age group.

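### Site is named as an adjustment covariate although each practice delivers only one strategy; entered as a fixed effect beside group, it makes the group effect non-estimable in the only planned outcome adjustment

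*Protocol article*

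**What the plan says.** All references are to the protocol article.

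- **Primary analysis** (*Analysis for the primary outcome*): the difference in completion between groups "will be examined for the primary outcome by a test of proportions". No covariates and no practice term are mentioned.
- **Adjustment** (same section): a sensitivity analysis is meant to allow for imbalance between the groups at the outset. The article states: "we will assess if the differences in site, demographic, and comorbid conditions impact the observed group differences by multinomial logistic regression". Site stands in one list with patient demographics and comorbidity.
- **Outcome** (*Statistical considerations*): "The primary outcome measure is the proportion of patients in each group who dial the phone number and complete the test within 2 months". For each patient this is yes or no.
- **Allocation** (*Patient recruitment and informed consent*): eligible patients "receive a study packet appropriate for the intervention group to which that practice site is assigned". The layout is "110 per practice in each of the six participating practice sites, two practices per intervention arm", and *Statistical considerations* repeats it: "In each of six practices, it is expected that 110 patients will receive a study packet, with two practices per intervention arm".
- **Randomisation** (*Discussion*): "we chose not to randomize the patients or the sites for pragmatic reasons".

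**The concern.** A covariate can be adjusted for only if it varies within the groups being compared, or if a further assumption supplies the missing information. Site does not meet the first condition. A patient's practice tells you the group exactly, so no practice shows what a second strategy would have done there. A model with both group and fixed site effects asks the data to split one quantity in two.

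The article itself expects practices to recruit different kinds of patients, and it offers this regression in response. Practices were also placed in groups partly by how able and willing they were to run the strategy (*Site recruitment and context*), which could itself be related to completion. If the model is programmed as the sentence most naturally reads, the adjusted result is either missing or an artefact of coding. The reader is then left with the unadjusted comparison and no usable check on it.

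**Working it through.** **The plan's own figure.** The article gives no figure for the adjusted model. Its nearest one is power above 99% for Group 3 against Groups 1 and 2 (*Sample size*: 25%, 50% and 80% completion, 200 per group, two-sided alpha 0.05, patients treated as independent). It reproduces: about 100% for 80% against the pooled 37.5%, and above 99.99% for 80% against 50%. Nothing below turns on it.

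**Step 1: estimability with fixed site effects.** Number the practices 1 to 6, with 1 and 2 in Group 1, 3 and 4 in Group 2, and 5 and 6 in Group 3. The model has an intercept, 2 group indicators (Groups 2 and 3) and 5 site indicators (practices 2 to 6), so 1 + 2 + 5 = 8 columns. Two exact identities hold:

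- Group 2 indicator = site 3 + site 4
- Group 3 indicator = site 5 + site 6

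The rank is therefore 8 − 2 = 6. Numerically, with 6 × 110 = 660 rows, the rank is 6. Intercept plus site alone already has rank 6, so group adds 0 degrees of freedom. Group 3 − Group 1, Group 2 − Group 1, and Group 3 minus the mean of Groups 1 and 2 are all non-estimable. Three patient covariates raise the columns to 11 and the rank to 9, so the deficiency of 2 remains.

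**Step 2: what a printed coefficient would mean.** Binary outcomes were simulated once at the planned rates, with no true difference between practices in the same group. Three of the six site indicators were then left out in three different ways:

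| Site indicators left out | Log OR, Group 2 vs 1 | Log OR, Group 3 vs 1 | Log-likelihood |
|---|---|---|---|
| 2, 4, 6 | 1.37 | 2.73 | −376.04 |
| 1, 3, 5 | 1.31 | 2.66 | −376.04 |
| 1, 4, 6 | 1.42 | 2.78 | −376.04 |

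The fit is identical and the estimates differ. Each coefficient compares one practice with one other; in the first row, the Group 3 coefficient is practice 6 against practice 2. The spread is small here because practices within a group were given the same true rate. Where they differ, it grows with that difference.

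**Step 3: models that can be estimated.** With group and patient covariates but no site terms, the group contrasts are estimable. With practice as a random effect they are also estimable, but only 6 − 3 = 3 between-practice degrees of freedom carry them. The two-sided 5% critical value is then 3.18 rather than 1.96.

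**Step 4: the word multinomial.** Multinomial and binary logistic regression were fitted to the same yes/no outcome. Coefficients and standard errors differed by less than 1e-14, so they are the same model.

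**Step 5: how much wider the interval becomes.** The article calls the intra-class correlation (ICC) unknown, so 0.01 to 0.10 is assumed here. The approximate widening against an analysis of independent patients is √(1 + 109 × ICC) × 3.18/1.96:

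| Assumed ICC | Design effect | Interval width, times naive |
|---|---|---|
| 0.01 | 2.09 | 1.45 × 1.62 = 2.3 |
| 0.05 | 6.45 | 2.54 × 1.62 = 4.1 |
| 0.10 | 11.90 | 3.45 × 1.62 = 5.6 |

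**The case against.** The strongest reply is that the article does not fix the failing model. It does not say that site enters as indicators, that all factors share one model, or that site means anything more than characteristics such as specialty and size. Such detail often waits for an analysis plan, which is not shown. This stands in part: a reader might infer that the adjustment cannot work at all, and the text does not support that, because Step 3 gives two estimable versions. But the article does more than stay silent. It names site in parallel with patient covariates and mentions neither a random effect nor a cluster-level analysis, so the most natural reading is the one that fails.

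Three other strong readings are tempting and do not hold.

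- **Multinomial regression cannot handle a yes/no outcome.** It can (Step 4).
- **If group is the multinomial response, completion is not adjusted at all.** The odds ratio is symmetric, so with completion and the covariates as predictors the completion coefficient is still a covariate-adjusted log odds ratio. In a simulated example with one confounder and n = 60,000, both directions gave 1.08 (Group 2 vs 1) and 2.48 (Group 3 vs 1), against 1.23 and 2.76 unadjusted. Site indicators would be no more usable in that direction.
- **This model is the only protection against confounding.** Practices are balanced on three factors at the design stage, and imbalance in patient characteristics will be examined (*Discussion*). Neither step adjusts the outcome comparison, which is the narrower statement made here.

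It is also fair to say that the regression is labelled a sensitivity analysis, and that the *Discussion* is open about the lack of randomisation and about needing ten or more clinics per arm for an adequately powered cluster-randomised trial.

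**Conclusion.** The point holds in a limited form. If site enters as a fixed covariate beside group, every group contrast is non-estimable (8 columns, rank 6). This follows from the allocation alone and does not depend on sample size, completion rates or ICC. It affects the only planned adjustment of the outcome comparison in a non-randomised study, so the sentence should be corrected before analysis.

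The primary test of proportions can still be run and does not depend on this model. A reader might conclude that the adjusted estimate must become the primary one. The documents do not require that; it would be a preference. The label multinomial needs clarifying but does not invalidate the analysis. The interval widths in Step 5 rest on assumed ICCs and a normal-theory approximation, and they show only the likely order of the cost.

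**What to change.** Replace the sentence on multinomial regression with text to this effect:

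> As a sensitivity analysis, tele-HS completion within 2 months (yes/no) will be modelled by binary logistic regression on group and patient covariates (demographics and comorbidity, listed by name). Site will not be entered as a fixed effect. Practice will be treated as the cluster, with small-sample inference on 3 between-practice degrees of freedom. The adjusted result will be reported beside the unadjusted one.

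Practice can be handled in either of two ways, and one should be chosen in advance:

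1. a logistic mixed model with a practice random effect; or
2. a two-stage analysis: fit patient covariates without group, form one residual (observed minus expected completion) per practice, and compare the six residuals between groups on 3 degrees of freedom.

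Add a sentence that two non-randomised practices per group cannot fully separate site from strategy. A random practice effect gives more honest uncertainty but does not remove confounding at practice level.

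The cost is wording, minor programming and a wider interval for the adjusted estimate. No change to recruitment or data collection follows from this point.

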## Discussion

This study is designed to answer real-world questions in hearing health care: what primary care model is best for motivating adults ages 65–75 years to complete a tele-HS and follow-up for medical evaluation and care if warranted, and how accurate are assessments of red flag conditions from patient, PCP and audiologists? We further assess barriers to implementation including attitudes, perceptions, cognitive impairment and costs in order to guide future implementation research that could test discrete implementation strategies [39]. We designed this study to begin with patients’ subjective assessment of the presence or absence of significant hearing loss in order to consider necessary education and behavior change strategies that could be tested for inclusion in the context of routine care. The burden of hearing loss at the individual, familial, healthcare, community and societal levels is immense, and increasing as the US population of older adults increases; yet, the population and public health impact is currently underestimated because too few people are screened, referred and treated.

NASEM convened an expert committee to study and provide recommendations in 2016 for improving the affordability and accessibility of hearing health care for adults in the US. Institutional, technological and regulatory changes are recommended [16]. Beyond hearing aids and assistive technologies, the committee importantly acknowledged that assessment of hearing difficulties and loss, diagnosis of underlying conditions, treatment and counseling are often overlooked. Our study addresses this gap directly by testing different approaches as part of routine primary care and measuring the percent of patients who follow recommendations as they transition in care to meet their needs. Factors associated with refusal or discontinuation of care will be informative for guiding uptake and future implementation efforts.

This study will establish evidence for conditions that should be contraindicated for hearing aid fitting and the impact of the most common red flag condition, cerumen, on hearing thresholds. Although the FDA has eliminated the requirement for medical evaluation of red flag conditions as it was in place without evidence to support it, we are still without research on these conditions as contraindications. The ‘red flag’ requirement for education of potential hearing aid users remains in place to ensure users are aware that there may be a medically treatable cause of their hearing loss. Our findings will help inform both practice and policies for audiologists, hearing aid dispensers and labeling of amplification devices.

As part of our implementation-effectiveness design, we chose not to randomize the patients or the sites for pragmatic reasons. Patient randomization to the intervention would mean that all clinics would have to be able to employ each screening strategy. In a real-world scenario, clinics will likely implement only one screening strategy. Clinic randomization is also not performed due to budget limitations for involving a high number of clinics and an unknown intra-class correlation for an adequately-powered cluster randomized trial, which would require at least 10 clinics per intervention arm. Site-level implementation allows us to train providers and measure costs of implementing a new approach as part of standard of care for this patient population. A site-level design increases pragmatism, feasibility of PCP engagement, and simplifies the patient recruitment process in comparison with a patient-level or patient-randomized design. We aim to achieve balance in site-level characteristics (PCP specialty, number of providers and eligible patients) and the number of patients is held constant across sites and interventions arms. However, we will plan to evaluate for imbalance in patient characteristics (race/ethnicity, sex) of study participants and non-participants between groups, and demographics of the study sample (approached, declined, enrolled) to the overall practice demographics for this age group.

In conclusion, our study addresses critical gaps in hearing health care. If successful, we will identify a primary care-based approach that increases uptake of tele-HS and medical follow-up. The design of our study will accelerate translation into practice and establish the foundation for widespread large implementation and future research to reach medically underserved populations. Hearing is vital to daily function and participation at home, in the workplace and in the community; it is a public health imperative that research continues to advance access and accessibility to hearing health care services and technologies.

